## Study Outcomes

The primary study endpoint is the rate of incident (new or progressive) radiological HT. The secondary endpoint is the rate of symptomatic HT, defined as intracerebral hemorrhage within and beyond infarcted brain tissue with PH > 1/3 the volume of the ischemic infarct (Class 2 in HBC) associated with clinical deterioration (worsening of NIHSS score by ≥4 points) within 30 days of treatment initiation (18, 22). Other secondary endpoints are recurrent ischemic stroke within 90 days of randomization, recurrent sub-clinical infarcts on follow up CT at 7 ± 2 days post edoxaban initiation, systemic hemorrhagic complication rate within 90 days of randomization, NIHSS at day 7 and 90, mRS score at day 7 and 90, favorable mRS at day 90, and mortality within 90 days, quality of life at 90 days assessed by EQ-5D and VAS, and ability of leukocyte RNA to predict HT.

## Sample Size Estimates

Based on previous open label studies of DOAC use in acute stroke, the rate of symptomatic HT is likely to be nil, which is why we have made this a secondary endpoint. We have previously demonstrated the rate of asymptomatic HT in serial imaging studies to be as lower as 3% in CT-based studies (23, 24) and up to 13% in MRI based studies (25). There are no data related to the difference in asymptomatic HT rates in patients randomized to early vs. late DOAC initiation. Our aim is to determine the event rates in these two groups with reasonable precision.

A sample size of 150 patients, randomized 2:1 (≤5 days:6–14 days) will allow detection of an asymptomatic hemorrhage rate of 3% (95% CI 0.6–8.5%) in the early treatment arm (*n* = 100) and 4% (95% CI 0.5–13.7%) in the late treatment arm (*n* = 50). Thus, we will have confidence interval width of a maximum of 13.7%, allowing enough precision to demonstrate the safety of early treatment. The rationale for adopting a 2:1 randomization approach is to increase the precision around the estimate of safety in the early treatment arm, without substantively losing power.

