### Randomization

Eligible patients will be randomized 2:1 following open label simple randomization procedure to early (≤ 5 days) or delayed (6–14 days) edoxaban initiation via a centralized web-based randomization process, Research Electronic Data Capture (REDCap, Vanderbilt university) (19, 20). After randomization to early or delayed arms, the decision to time the edoxaban initiation within the specific arm will be at the treating physician's discretion.

The rationale for the specific timing of treatment, within the randomization window, will also be recorded by surveying the treating physician in each case.

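### The 13.7% given as the maximum confidence interval width is the delayed arm's upper limit, is not a maximum, and does not support the claim about early treatment

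*Protocol article*

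**What the plan says.** Sample Size Estimates in the protocol article starts from "A sample size of 150 patients, randomized 2:1", that is, 100 early and 50 delayed. It gives the precision expected in each arm: "asymptomatic hemorrhage rate of 3% (95% CI 0.6–8.5%) in the early treatment arm" and "4% (95% CI 0.5–13.7%) in the late treatment arm". From these it concludes: "Thus, we will have confidence interval width of a maximum of 13.7%, allowing enough precision to demonstrate the safety of early treatment".

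The same section says that the aim is to estimate the event rate in each group. It reports earlier serial-imaging rates "as lower as 3% in CT-based studies (23, 24) and up to 13% in MRI based studies". The Imaging Protocol section says that baseline and day 7 imaging are now by CT.

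Study Outcomes defines the endpoint: "The primary study endpoint is the rate of incident (new or progressive) radiological HT". The Introduction states a comparative hypothesis, that early initiation does not raise HT rates relative to delayed initiation. Statistical Analysis reports a rate with a 95% CI for each group and tests the difference in proportions with Fisher's exact test.

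**The concern.** The two printed intervals and the concluding sentence do not agree. An interval from 0.5% to 13.7% cannot be 13.7 points wide. The width of a binomial interval also grows as the observed rate rises towards 50%, so a width computed at one assumed result does not bound the width the trial will obtain. Finally, the number comes from the delayed arm, while the conclusion drawn from it concerns early treatment.

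This sentence is the only link between the sample size and the claim that the trial can show safety. The Abstract says the results will feed the sample size calculation of a definitive trial, so readers are likely to rely on the stated precision.

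**Working it through.** **Inputs.** Arm sizes 100 and 50, rates 3% and 4%, and the 95% level come from Sample Size Estimates. The event counts 3/100 and 2/50 follow from 0.03 × 100 and 0.04 × 50. The 13% scenario is the article's MRI figure. In the delayed arm 13% of 50 is 6.5, so 6/50 and 7/50 bracket it.

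**Step 1: reproduce the printed intervals.** Exact (Clopper-Pearson) limits for x events in n are the 2.5% quantile of Beta(x, n − x + 1) and the 97.5% quantile of Beta(x + 1, n − x).

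- 3/100: 0.62% to 8.52%
- 2/50: 0.49% to 13.71%

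Both match the article.

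**Step 2: the width.** Width is upper limit minus lower limit.

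- Early arm: 8.52 − 0.62 = 7.9 points
- Delayed arm: 13.71 − 0.49 = 13.2 points

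Other methods do not give 13.7 as a width for 2/50 either: Wilson gives 1.10–13.46% (12.4 points), and Wald truncated at zero gives 0–9.43% (9.4 points). The 13.7% is the exact upper limit.

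**Step 3: is it a maximum?** Exact intervals at other results:

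| Result | 95% CI (%) | Width (points) |
|---|---|---|
| 2/50 | 0.49–13.71 | 13.2 |
| 3/50 | 1.25–16.55 | 15.3 |
| 4/50 | 2.22–19.23 | 17.0 |
| 6/50 | 4.53–24.31 | 19.8 |
| 7/50 | 5.82–26.74 | 20.9 |
| 13/100 | 7.11–21.20 | 14.1 |

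One event more than assumed already exceeds 13.7. If the true delayed-arm rate is 4%, the chance of 3 or more events in 50 is

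1 − [0.96^50 + 50(0.04)(0.96^49) + 1225(0.04²)(0.96^48)] = 1 − (0.130 + 0.271 + 0.276) = 0.32.

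So even under the article's own assumption the stated maximum is exceeded about one time in three.

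**Step 4: precision of the comparison.** The Newcombe interval for early minus delayed uses the Wilson limits, 1.03–8.45% for 3/100 and 1.10–13.46% for 2/50, and the difference 3 − 4 = −1 point.

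- Lower: −1 − √[(3 − 1.03)² + (13.46 − 4)²] = −1 − 9.66 = −10.7
- Upper: −1 + √[(8.45 − 3)² + (4 − 1.10)²] = −1 + 6.17 = +5.2

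The width is 15.8 points. Agresti-Caffo gives −9.2 to +5.5 (14.7). Wald gives −7.4 to +5.4 (12.8), but it is a poor approximation with 3 and 2 events.

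**The case against.** The strongest defence is that the mislabelling moves the figure by only 0.5 point, that both intervals are computed correctly, and that 'maximum' may mean no more than the wider of the two intervals just listed. The first two parts stand. The third rescues the word but not the number, since the wider of the two widths is 13.2. The sentence is also phrased as what the trial will have, which a single extra event would break.

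A second defence is that the section declares a per-arm estimation aim, and the Limitations say the trial is not powered for clinical outcomes. This stands too. A reader might infer that a sample size built on per-arm intervals is wrong because the hypothesis is comparative. The documents do not support that: per-arm intervals fit the declared aim, and the fault lies in the conclusion drawn from them.

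Three further inferences go too far:

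- **13% as the planning rate.** It is the MRI figure, and imaging is now by CT. It serves only as an upper scenario, and the failure of 'maximum' does not depend on it.
- **The endpoint mismatch as a numerical error.** The calculation refers to asymptomatic haemorrhage, whereas the endpoint is new or progressive radiological HT. Symptomatic HT is expected to be nil, so the two are close, and the article gives no figure for the effect of counting progression.
- **Uncertain arm sizes.** Allocation "following open label simple randomization procedure" means 100 and 50 are expected sizes, not guaranteed ones. Using planned sizes in such a calculation is normal, and departures can go either way. No change is asked for on this account.

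**Conclusion.** The point holds as an error in the stated precision and in the conclusion resting on it. The delayed-arm width is 13.2 points at 2/50, and 13.7% is that interval's upper limit. It is not a ceiling: the width is 15.3 points at 3/50, 17.0 at 4/50, and about 20–21 if the rate approaches the MRI figure, at which even the larger arm reaches 14.1.

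For early treatment the relevant per-arm figure is the early arm's own interval, 0.6–8.5%, which is narrower than the number quoted. For the comparison, the interval at the planned result is about 16 points wide and reaches +5.2 points. That is compatible with early initiation being somewhat worse, so the claim of enough precision to show safety is not supported.

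These figures assume arms of exactly 100 and 50, the event counts implied by the stated rates, exact per-arm intervals, and the Newcombe method for the difference. With the other methods tried, the width of the difference interval is 12.8 to 14.7 points. Nothing here shows that the sample size is unsuitable for estimating per-arm rates.

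**What to change.** Replace the concluding sentence of Sample Size Estimates with wording such as:

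> At 3/100 events the early-arm 95% upper limit is 8.5% (width 7.9 points). At 2/50 the delayed-arm upper limit is 13.7% (width 13.2 points), and the width would rise to about 20–21 points if the rate approached the 13% seen with MRI. At 3% versus 4% the 95% CI for the difference between arms is about 16 points wide (Newcombe). The trial estimates incident (new or progressive) HT rates in each arm with this precision.

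Delete 'maximum' and the claim that the precision is enough to show safety.

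The cost is a text correction. Sample size, allocation, endpoint and analysis stay as they are. The stated precision becomes less favourable for the delayed arm at higher rates and for the comparison, and more favourable for the early arm than the single figure now suggests.

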## Discussion

This randomized controlled trial (RCT) is the first step in advancing the knowledge of the safety of early vs. delayed anticoagulation after ischemic stroke in patients with AF. In our pilot safety studies with rivaroxaban, dabigatran, and apixaban we observed low rates of symptomatic HT when these DOACs were initiated within 14 days of symptom onset (23–25). While encouraging with respect to the safety of early DOAC initiation, these studies are far from definitive. Several trial protocols have been published and/or registered for the safety and efficacy of early vs. delayed anticoagulation after ischemic stroke in patients with AF (26–28). Patients in these trials are randomized to DOAC initiation as early as 24 h and up to 5 days after onset, or delayed initiation 6–14 days. The primary endpoint in these trials is the composite of recurrent ischemic stroke and symptomatic HT. Patient allocation to the treatment arms in most of these trials is determined by stroke severity and/or size. Ongoing trials include TIMING (Timing of Oral Anticoagulant Therapy in Acute Ischemic Stroke With Atrial Fibrillation: a Prospective Multicenter Registry-based Non-inferiority Randomized Controlled Clinical Trial, NCT02961348) (27), ELAN (Early vs. Late Initiation of Direct Oral Anticoagulants in Post-ischaemic Stroke Patients With Atrial fibrillation, NCT03148457), START (Optimal Delay Time to Initiate Anticoagulation After Ischemic Stroke in Atrial Fibrillation, NCT03031928) trials, OPTIMAS (OPtimal TIming of Anticoagulation After Acute Ischemic Stroke, NCT03759938) and AREST (Apixaban for Early Prevention of Recurrent Embolic Stroke and Hemorrhagic Transformation, NTC02283294).

Edoxaban is the newest drug in the DOAC class. Although equipoise exists with respect to timing of initiation of all the DOACs, a design utilizing all four drugs introduces additional confounding factors. A novel aspect of this RCT is to identify RNA transcript as well as clinical and imaging predictors of HT after AF related stroke. If a biomarker of HT risk can be identified, it may be useful in guiding anticoagulation timing after acute cardioembolic stroke. A standardized documentation of HT rates on follow-up CT as objective assessment criteria will be employed in this study. This method is missing from most studies of early anticoagulation.

### Limitations

The amended protocol limits follow-up imaging to CT, making it highly likely that we will under-estimate the true rate of recurrent sub-clinical infarcts. This trial is not powered to detect differences in clinical outcomes, including symptomatic HT and recurrent infarction. Dichotomization at 5 days leaves a considerable discretionary range within which clinicians can initiate edoxaban. In cases where the period of equipoise is narrower, i.e., day 0 vs. day 2–3, this may be relevant. Stratified randomization can address this to an extent, but as we are assessing radiological HT event rates, a more pragmatic approach was chosen for this trial.

### Trial Status

Enrolment of patients started in November 2018 and study completion is estimated in December 2023. Protocol version 4.0 was approved on 14 January 2021.

## Conclusion

Objective evaluation criteria such as systematically acquired imaging assessment of HT is required to understand the true effect of DOAC timing. These data are critical to developing future efficacy trials. Accurate and objective predictors of HT, including novel biomarkers, will also help refine future trial inclusion/exclusion criteria.

## Ethics Statement

This protocol was approved by University of Alberta Human Research Ethics Committee. The patients/participants or substitute decision maker will provide written informed consent to participate in this study.
